### Blood sampling and analysis

In all study parts, a blood sample (approx. 70 μl) is collected with capillary tubes after puncturing the finger bulb using safety lancets. Blood glucose as well as blood lipids (triglycerides, high-density lipoprotein cholesterol (HDL)) is analyzed simultaneously using a portable point-of-care analyzing device. During the pilot study, three different commercially available portable point-of-care analyzers (Alere Cholestech LDX, Alere GmbH, Germany; Samsung LABGEO, Samsung Healthcare, South Korea; CardioChek, PTS Diagnostics, USA) are initially compared and validated versus a certified reference laboratory including analysis of test-retest reliability and variability. The measurement device with the best reliable results for blood parameter analysis and MetS diagnosis is picked for further usage during part A and part B. Hb1Ac is also measured by using a point-of-care analyzer (Quo-Test A1C Test Kit, EKF-diagnostic GmbH, Germany).

In part B, blood samples are additionally taken from an antecubital forearm vein using a disposable needle and vacutainer. Blood is centrifuged immediately and serum samples are stored cooled for later additional analyses in a stationary laboratory, if necessary.

### Blood pressure measurement and anthropometrics

In all study parts, the systolic and diastolic blood pressure is measured using a manual sphygmomanometer and a stethoscope, mainly on the left arm, in the seated position after 5 min rest. Measurement of waist circumference is performed by using a non-stretching measuring tape and by obtaining the midpoint between the lowest rib and the top of the iliac crest of the unclothed upper body according to WHO guidelines [54]. The body weight is assessed using an electronic digital scale.

In part B, the body composition is estimated after measuring skinfold thickness using Harpenden calipers (Baty International, UK). Body fat percentage is calculated using ten sites with the equation from Parizkova et al. [55] and using four sites with the method according to Durnin et al. [56]. All measurements are done by a trained health care professional.

### Resting and exercise electrocardiogram

In part B, a bike ergometer (Ergometer ebike comfort, ergoline GmbH, Germany) with the Custo cardio 200 system (Custo med GmbH, Germany) are placed into the van enabling the conduction of a 12-lead resting and exercise electrocardiogram (ECG). A resting ECG is performed while the participant is sitting on the bike ergometer. The protocol for the exercise ECG includes the following: start cycling at 50 W and increase of the workload with 25 or 50 W every 3 min, termination because of exhaustion or other complaints of the participant. After the exercise ECG, the participant continues cycling for 3 min at 50 W and afterwards stays sitting on the bike for two additional minutes while heart frequency and blood pressure is checked.

### Questionnaires for assessment of socio-economic data, physical activity, and psychometric data

In part A, all participants are asked to fill in self-administered paper-pencil questionnaires about their sociodemographic basic information, perceived stress during the last month (PSS-4) [40], questions about life events within the last 3 months [35], and the physical activity (IPAQ-Short Form) [41]. After detailed instruction by a member of the study team, the IPAQ-Short Form is completed independently by the participant. A member of the study staff is always available to answer any questions that may arise during the completion of the questionnaires.

In part B, a self-administered paper-pencil questionnaire is filled in to screen for presence and severity of depression (PHQ-9) [42]. The “Montreal Cognitive Assessment” (MoCA) [43] is used by the trained physician for detection of mild cognitive impairment. The telephone interview of part B, for participants who are not eligible to the mobile examination, comprises questions about medical history, life style factors (self-reported), alcohol consumption (frequency, quantity, and type of drinks [36]) and smoking (frequency and quantity), urbanity [37], utilization of the health system (standardized single questions on distance to and consultations of general practitioner, medical specialists and hospital, utilization of health care programs, health insurance [38, 39]), and changes in health behavior after part A, as well as validated questionnaires for comorbidity (CCI) [44], depression (PHQ-8) [45], amnestic mild cognitive impairment (TICS-M) [46], social support (BSSS) [47], stress perception (PSS) [40], childhood trauma (CTS) [48], affect (PANAS) [49], psychological well-being (PWB) [50], musculoskeletal complaints such as (back) pain (CPG, BPI) [51–53], and the risk of developing chronic pain (RSI) [35]. Trained interviewers make an appointment in advance to guarantee a quiet setting for the telephone interview that is limited to 30 min.

### Consulting on nutrition and physical activity

After finalization of part A routine, the participants are advised verbally and by a flyer on recommendations about healthy nutrition and regular physical activity to prevent either the MetS (primary prevention) or the development or manifestation of its secondary diseases (secondary and tertiary prevention). Information is provided by the health care professional and is based on the recommendations of the German Nutrition Society (e.g., eat several servings of vegetables and fruits daily; prefer whole grain products; reduce sugar and salt intake; prefer vegetable oils; drink water or other calorie-free beverages) [57], as well as the WHO guideline for health-promoting physical activity (e.g., do at least 150 min of moderate-intensity aerobic physical activity per week; muscle-strengthening activities involving major muscle groups on 2 or more days per week) [58].

In part B, the participants receive individualized nutritional counseling from the physician. In addition, some simple sports exercises are demonstrated by the trained health care professional directly on site. These exercises use the participant’s own body weight, address core, and extremity strength (e.g., bridging, heel drop exercise, air cycling, wall push-ups) and can be performed independently after brief instruction. The practical instructions are supported by an illustrated flyer.

### Outcomes

Outcome of the pilot study is to evaluate the transfer of clinical, stationary routines into mobile examination units and to test the reliability and validity of the diagnosis of MetS and its secondary diseases in the mobile setting

In study part A, the “Mobile Brandenburg Cohort” is established by gathering a demographically representative study population via spontaneous recruitment. Central outcome of study part A is the prevalence of MetS and its components in this (rural) sample in Brandenburg. Main outcome of study part B is the validation of the MetS screening by medical diagnosis as well as the prevalence of its previously undiagnosed secondary diseases.

To reveal causal, risk, and moderating factors of MetS in Brandenburg, possible associations of MetS with socio-demographic data, psychometric parameters, and life style factors (e.g., socio-economic status, urbanity, social support, physical activity, perceived stress, life events; part A) as well as clinical and psychological parameters (e.g., comorbidities; part B) will be investigated.

The feasibility of the mobile measurements for MetS (part A) and secondary diseases (part B) in the patient-centered (mobile) setting will be evaluated. The following criteria are defined for success: In the pilot study, the mobile setup is evaluated by valid and reliable measurements of the MetS components with point-of-care analyzers applying conventional scientific criteria. The established diagnostics procedure is tailored to take maximal 20 min (on average) for part A and 75 min (on average) for part B and will be examined. For part A, at least 15 participants per measurement day, and for part B, at least 4 participants per measurement day are defined as a success. The feasibility assessment encompasses also qualitative criteria to evaluate an optimal balance between effort (approach, staff) and benefit (participation in the study).

By determining the rates of newly identified cases of MetS (part A) and indications for secondary diseases (part B), we will determine the usefulness of the mobile laboratory developed in the pilot study. This will help to reveal new ways for early diagnostic and prevention of secondary diseases in a patient-centered (mobile) care setting.

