### Participants

To be eligible for part A, adults (men and women) with an age between 40 and 70 years will be recruited. As the study aims to implement prevention strategies to reduce morbidity and mortality of the population due to MetS, the target population for inclusion are persons with emerging risk for MetS, but less probable presence of (multiple) manifested secondary diseases. Therefore, the age range was chosen to reach participants within the working and retirement age that feature a number of age-related risks for the presence of MetS and for development of its secondary diseases [29, 30]. To be eligible for part B, participants have to be diagnosed with MetS in part A, but have to have no (known and diagnosed) secondary disease. To be eligible for all study parts, participants have to be able to understand the study information and must provide written informed consent for each part.

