### Recruitment strategy

In part A, a passive recruitment strategy will be applied with a target population of all residents of Brandenburg that voluntarily approaches to the mobile diagnostic units [31]. Participants will be recruited at different locations in Brandenburg by setting up the mobile diagnostic unit in mainly rural areas far from metropolitan regions. In order to reach as many people as possible, targeted public relations work will be carried out and the mobile study unit is to be placed at market places and at events such as health days and festivals. Cooperation with companies and public administrations is planned in order to make the study known to their employees and encourage them to participate. Announcements will be done by advertising posters, articles in local newspapers and internal newsletters in companies, reports at local radio stations, and at online event calendars of communities and towns. On site, interested passers-by and participants will be directly addressed and recruited spontaneously.

For part B, potentially eligible participants who were diagnosed with MetS in part A and give consent to be re-contacted, will be recruited by telephone. Eligible persons will be allocated to the mobile examination or telephone interview in study part B.

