### Data management and statistics

The study is conducted in compliance with the EU’s General Data Protection Regulation (GDPR) [59]. Participant’s data will be processed pseudonymized. All data will be first documented in paper-pencil form and then entered in an electronic data base for further analyses. Programed plausibility checks (including, i.e., valid value checks and range checks) will be performed after assessment completion. All data are to be evaluated descriptively (i.e., mean, standard deviation, median, ranges, frequencies) to evaluate prevalence of MetS and of the respective risk factors (in the full study cohort and in defined subgroups, e.g., according to age and recruitment regions). The data sets will be evaluated conducting full case and complete case analyses. Paired *t* tests and Pearson’s Chi-squared tests are planned to evaluate any gender differences to all predictor and outcome variables. To evaluate the association of MetS with other assessed factors and variables (e.g., anthropometric parameters, age, sex, urbanity, physical activity, stress perception, social support, identified abnormalities, or diseases), inferential statistics (e.g., regression analysis, ANOVA), and cluster analyses are planned.

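### Part A claims demographic representativeness for a self-selected walk-in sample, so its descriptive MetS prevalence is at risk of bias when read as a figure for Brandenburg

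*Protocol article*

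**What the plan says.** Four places in the protocol article bear on this.

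- **Outcomes.** Part A establishes the cohort "by gathering a demographically representative study population via spontaneous recruitment". The next sentence makes the prevalence of MetS and its components the central outcome, worded for this (rural) sample.
- **Recruitment strategy.** The method is given as follows: "a passive recruitment strategy will be applied with a target population of all residents of Brandenburg that voluntarily approaches to the mobile diagnostic units". On placement, "the mobile study unit is to be placed at market places and at events such as health days and festivals". On employers, "Cooperation with companies and public administrations is planned". Sites are mainly rural and away from metropolitan regions, and people passing by are approached on the spot. No sampling frame, quota, random selection or record of those who decline is described.
- **Data management and statistics.** "All data are to be evaluated descriptively", by means, medians, frequencies and the like, to obtain prevalence in the full cohort and in subgroups such as age and recruitment region. No weighting or standardisation is named.
- **Abstract, aims (end of Background) and Discussion.** These present the result as MetS prevalence, with its causes and influencing factors, in Brandenburg.

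**The concern.** Representativeness is a property of how people enter a sample, and the article asserts it for a procedure that does not control entry. Who is counted depends on who visits a market, health day or festival, who works for a cooperating employer, and who is interested enough to stop. Age, employment, health awareness and mobility plausibly affect both attendance and MetS.

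The claim concerns the population behind the central outcome of part A and behind a cohort meant for later longitudinal work. A reader who accepts it would take the sample frequency as the state's prevalence at age 40 to 70, and would take a narrow sampling error as the whole uncertainty. A large sample reduces sampling error but leaves selection error unchanged.

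**Working it through.** **1. The plan's own figure.** Sample size determination gives 5000 participants, a prevalence of 22% and about 1100 cases: 5000 × 0.22 = 1100, which reproduces. At the 3,931 enrolled (Study status), 3,931 × 0.22 = 865. The article states no confidence interval or precision target, so there is no precision figure to reproduce.

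**2. Sampling error alone.** The 95% half-width under simple random sampling is 1.96 × √(p(1 − p)/n). With p = 0.22:

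- n = 5000: 1.96 × √(0.22 × 0.78/5000) = 1.15 points
- n = 3,931: 1.96 × √(0.22 × 0.78/3931) = 1.29 points

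**3. Effect of the attendees' age mix.** Assumed, not in the document: prevalence of 15, 25 and 35% in the three decades from 40 to 70.

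| Age mix (youngest / middle / oldest decade) | Calculation | Unstandardised prevalence |
|---|---|---|
| Equal thirds | (15 + 25 + 35)/3 | 25.0% |
| 20 / 35 / 45% | 0.20 × 15 + 0.35 × 25 + 0.45 × 35 | 27.5% |
| 45 / 35 / 20% | 0.45 × 15 + 0.35 × 25 + 0.20 × 35 | 22.5% |

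The shift is 2.5 points either way, about twice the 1.29 points in step 2 (2.5/1.29 = 1.9). Standardisation would remove this part.

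**4. Effect of volunteering.** Let r be the attendance rate of people with MetS divided by that of people without. The observed prevalence is P·r/(P·r + 1 − P). With an assumed true P of 22%:

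- r = 0.8: 0.176/(0.176 + 0.78) = 18.4%
- r = 1.25: 0.275/(0.275 + 0.78) = 26.1%
- r = 0.93: 0.2046/(0.2046 + 0.78) = 20.8%
- r = 1.07: 0.2354/(0.2354 + 0.78) = 23.2%

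So a difference in attendance of about 7% moves the result by about 1.2 points, roughly the whole half-width at n = 5000. Age-sex standardisation removes this only as far as attendance differs through age and sex.

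**5. Direction.** Recruitment through employers and health events could lower the figure, and attendance by people worried about their health could raise it. Nothing in the article settles which dominates.

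**6. Can the fix be done?** Age is known, since it determines eligibility and defines a planned subgroup. Sex is known, since the HDL and waist cut-offs in Table 1 differ by sex. An age-by-sex standardised estimate needs no further data from participants.

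**The case against.** The best defence is that the central outcome is worded as prevalence in this sample, that prevalence by age is planned, and that standardisation may sit in an analysis plan that is not shown. Much of this stands. The word crude does not appear in the article, so an unstandardised headline figure is an inference from the descriptive methods named. Nor can the figure be called biased: it is at risk of bias. But no analysis plan can make the recruitment representative. Age subgroups show heterogeneity without correcting the overall figure, and the sample wording sits beside statements about Brandenburg.

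Four stronger readings are tempting, and the document does not support them.

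- **Clustering makes the stated precision wrong.** No interval or standard error for prevalence is stated, and the handling of site is commonly left to an analysis plan. At n = 3,931, with an assumed 15 people per measurement day and intraclass correlation of 0.01 to 0.05, the design effect 1 + 14 × ICC is 1.14 to 1.70. The half-width rises from 1.29 to 1.38–1.69 points, which is modest beside plausible selection effects.
- **Tests between regions have inflated error rates.** Region appears only as a descriptive subgroup. The named chi-squared tests compare genders, which vary within a site, so the design effect for a cluster-level exposure does not apply to them.
- **The crude result is benchmarked against an age-standardised 22%.** The 22% is used only to project the yield of cases, and no comparison with it is planned.
- **Non-residents are counted.** Residents are the target under Recruitment strategy. The eligibility text ("adults (men and women) with an age between 40 and 70 years will be recruited") does not repeat this, but it is condensed, and no extent of non-resident enrolment can be derived.

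**Conclusion.** The representativeness claim is unsupported by the design described in the same article. That conclusion needs no assumption. It follows that the unstandardised MetS prevalence, if read as a figure for Brandenburg, is at risk of bias from the age-sex mix of attendees and from volunteer selection.

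Size and direction cannot be derived from the document. The 2.5-point shift rests on assumed prevalences by decade and assumed age mixes, and the volunteering figures rest on an assumed true prevalence of 22% and assumed attendance ratios. They show only that moderate departures from representativeness can match or exceed the sampling error of about 1.3 points at the enrolled number, and that more recruitment would not reduce them. A reader might go further and conclude that the reported prevalence will be wrong by a known amount, or that its precision is misstated. The article supports neither.

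**What to change.** 1. In Outcomes, delete the words demographically representative and describe part A as a convenience sample of volunteers at mainly rural sites.
2. Compare the age and sex distribution of participants with that of the Brandenburg population aged 40 to 70, taken from official statistics.
3. Report MetS prevalence directly standardised to that age-by-sex distribution, with the crude figure beside it.
4. State that standardisation leaves residual volunteer bias, and word any conclusion about Brandenburg accordingly.

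A secondary suggestion, not the correction of an error: if confidence intervals are reported, allow for recruitment site or day, for example with cluster-robust standard errors. Restricting the analysis to residents or reporting by type of site would also be informative, but only if residence and site type were recorded, which the article does not show.

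The cost is a little more analysis on variables already collected, slightly wider intervals and a weaker claim. Recruitment for part A has ended for the time being, so the change affects wording and analysis only.

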In part B, participants diagnosed with MetS in part A will be recruited for a later detailed examination to check for indications of secondary diseases of MetS. Part B examinations will be also done in a mobile examination unit close to the participant’s home by a health care professional together with a physician. A detailed medical history, a clinical examination and instrumental as well as questionnaire-supported diagnostics for internal, orthopedic, cardiological, and neurological-psychiatric abnormalities will be carried out. In addition, the participants will receive a detailed consultation on healthy nutrition and a prevention exercise program directly at hand. The whole mobile clinical examination and consultation of part B will take no more than approximately 60 min. Participants who will be not eligible to mobile examination for secondary diseases will be invited to a telephone interview comprising an assessment with questionnaires that provides comparable and advanced information to the part B examinations, if procurable.

In all study parts, the participants will get their test results instantly and, if necessary due to MetS diagnosis and abnormal parameters, they will be referred to their general practitioner or a responsible medical specialist for further diagnostics and treatment.

By collecting data on MetS and its secondary diseases using mobile diagnostic units at various locations throughout the state of Brandenburg, a “Mobile Brandenburg Cohort” is to be established which can be used for further follow-up measurements with a longitudinal approach.

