### Diagnosis of metabolic risk factors

In all study parts, the MetS diagnosis is based on the definition by Alberti et al. [9] (Table 1). The mobile diagnostic approach requires spontaneous recruitment throughout the day and participants will not be always in a fasted state prior to blood sampling. Therefore, the cut-off point for elevated blood glucose is adapted according to Schipf et al. [32]. For the lipid profile, it was shown that there is little difference between fasting and non-fasting values [33] and for the estimation of an initial risk and for MetS diagnosis, also non-fasting lipids are acceptable [34]. Moreover, the more stable and meal-independent glycated hemoglobin (Hb1Ac) will be determined. It provides additional hints about impaired long-term regulation of glucose metabolism as well as helps to meaningfully assess metabolic risk factors and lipid profile even in a non-fasted state [34].

**Table 1 Tab1:** Criteria for diagnosis of the metabolic syndrome according to Alberti et al. [9]

The presence of any 3 of the following 5 risk factors constitutes a diagnosis of MetS	
Measure	Cut points/criteria
Elevated blood pressure	Systolic ≥ 130 mmHg and/or diastolic ≥ 85 mmHg [or antihypertensive drug treatment]
Elevated triglycerides	≥ 150 mg/dl [or drug treatment for elevated triglycerides]
Reduced HDL-cholesterol	Males: < 40 mg/dl, females: < 50 mg/dl [or drug treatment for reduced HDL-cholesterol]
Elevated blood glucose	≥ 100 mg/dl (fasting) or ≥ 144 mg/dl (non-fasting)* [or drug treatment for elevated glucose/type 2 diabetes mellitus]
Elevated waist circumference	Population-/country-specific, according to IDF recommendation for people with European origin: males ≥ 94 cm, females ≥ 80 cm

Abbreviations: *IDF* International Diabetes Federation, *HDL* high density lipoprotein, *MetS* metabolic syndrome

*Adaption to non-fasting blood samples according to Schipf et al. [32]

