## Discussion

The study presented in this protocol will test the feasibility of new approach for mobile and near-to-home diagnostic to realize an early detection of risk factors and diseases linked to MetS in order to implement prevention strategies to reduce the morbidity and mortality of the population, especially in rural areas. The mobile setup will include time-, space-, and cost-efficient procedures which are to be predominantly performed by health care professionals (and physician-independent) and will lead to valid and reliable diagnostics of MetS and its pathophysiological consequences, which will be qualitatively equivalent to routine stationary examinations. In contrast to other mobile care and prevention ventures (e.g., mobile mammography van), walk-ins and spontaneous consultations enables a comprehensive access to precautionary and preventive health care.

According to the European policy for health and well-being [60], this mobile diagnostic approach should contribute to reduce health inequalities, strengthen public health, and ensure people-centered health systems and low-threshold access to prevention and health care. It should provide a complementary strategy for visiting a general practitioner and local health care providers. Thus, the mobile examination is the preliminary stage that enables an early connection to the health care system, if necessary. Individuals can be identified as persons at risk even before the onset of any disease and thus early prevention strategies can be initiated. Hence, only individuals who have been identified as requiring further diagnosis and treatment are referred to the relevant regional providers and consequently, only patients at risk and those with diseases are treated earlier, while persons without a risk profile are advised directly on primary prevention. In the long term, this strategy could complement the approaches discussed so far to increase medical capacity, reduce the physician shortage, and relieve the burden of the public health system [20, 61, 62].

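### Part B's main outcome, validating the MetS screening, claims more than re-examining only screen-positives can show; it should be restated as a confirmation rate

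*Protocol article*

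**What the plan says.** The Outcomes section of the protocol article gives part B two main outcomes: "Main outcome of study part B is the validation of the MetS screening by medical diagnosis as well as the prevalence" of secondary diseases not diagnosed before.

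The design of part B is set out elsewhere in the article:

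- **Who enters.** Under Participants: "participants have to be diagnosed with MetS in part A, but have to have no (known and diagnosed) secondary disease". Under Recruitment strategy, those approached are "potentially eligible participants who were diagnosed with MetS in part A and give consent to be re-contacted".
- **Criteria.** Under Diagnosis of metabolic risk factors: "In all study parts, the MetS diagnosis is based on the definition by" the cited consensus (Table 1). The same section notes that "participants will not be always in a fasted state prior to blood sampling" and therefore adapts the glucose cut-off. Table 2 refers the part B mobile MetS diagnosis back to Table 1 and lists no MetS measurement for the telephone interview.
- **Device and methods.** Under Blood sampling and analysis, the best-performing analyzer "is picked for further usage during part A and part B". Capillary sampling, manual blood pressure and waist measurement are common to all parts. Venous serum is added in part B, but it is stored and analysed only if necessary.
- **Between the visits.** Under Study design and flow, participants get their results at once and, if necessary, "they will be referred to their general practitioner or a responsible medical specialist for further diagnostics and treatment". Part A also ends with advice on nutrition and activity. Part B comes later, and the interval is not given.

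On validity more widely, the pilot outcome (and the first aim in the Background) covers the diagnosis of MetS and of its secondary diseases. The Discussion expects "valid and reliable diagnostics of MetS and its pathophysiological consequences, which will be qualitatively equivalent to routine stationary examinations". The only comparison with a reference that the article describes is the pilot's: three blood analyzers against a certified laboratory, with 50 participants.

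**The concern.** A screening procedure can fail in two ways: it can label people who do not have the condition, and it can miss people who do. Part B can speak only to the first. If a high proportion of positives is confirmed and reported under the name validation, a reader will take the mobile screening as shown to be accurate, although nothing has been learned about missed cases. For a programme meant to find people whom existing care does not reach, missed cases are the more important error.

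Even the first kind of error is seen indirectly. Repeating the same criteria on the same analyzer lets a systematic device error repeat and pass as confirmation. Advice, referral and the passage of time can change a participant's true state, and values selected for being high on one occasion tend to be lower on the next.

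The pilot and Discussion statements extend validity to secondary-disease diagnostics, for which no comparison with a reference is described.

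**Working it through.** **1. The plan's own figure.** Sample size determination: 5000 × 0.22 = 1100 expected positives, as stated. That leaves 5000 − 1100 = 3900 negatives, none of whom enters part B.

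**2. What part B can identify.** Let s be the screen-positive share, c the confirmed proportion among positives, and p the true prevalence. For this step, treat confirmation as perfect and representative of all positives.

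- True-positive share = s × c
- Sensitivity = s × c / p
- Missed cases per 5000 = 5000 × (p − s × c)

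Part B informs c only. The true prevalence p depends on the unverified negatives. Taking s = 0.22 (the plan's prevalence, reused here as the screen-positive share) and c = 0.90 (assumed) gives s × c = 0.198.

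| True prevalence p (assumed) | Sensitivity = 0.198/p | Missed cases per 5000 |
|---|---|---|
| 20% | 99% | 10 |
| 22% | 90% | 110 |
| 25% | 79% | 260 |
| 30% | 66% | 510 |
| 35% | 57% | 760 |

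Every row produces the same part B data. A larger part B would not separate them.

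**3. The confirmation rate is not a clean predictive value.** Suppose the true positive predictive value is v, a fraction r of true cases no longer meets the criteria at part B, and a fraction q of false positives is positive again. Then:

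- Observed confirmation = v(1 − r) + (1 − v)q

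With v = 0.80 (assumed):

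- r = 0.30, q = 0: 0.80 × 0.70 = 0.56
- r = 0, q = 0: 0.80
- r = 0, q = 1: 0.80 + 0.20 = 1.00

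Agreement is affected as well as disagreement. Table 1 counts drug treatment as meeting four of the five criteria, so treatment started after a falsely high part A reading would itself satisfy that criterion at part B.

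**4. Who contributes.** Only mobile attendees have MetS measured again. Study status reports 93 of them. With 3931 enrolled in part A, 3931 × 0.22 ≈ 865 positives would be expected, before removing those with known secondary disease, and 93/865 ≈ 11%. Sampling error is the smaller problem: an observed 90% of 93 has a 95% Wilson interval of 82.2% to 94.6%.

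**5. Whether the pilot fills the gap.** It does supply a laboratory comparison for the blood analytes. For MetS classification it is small. If its case mix were 22% (its composition is not stated), 50 × 0.22 = 11 cases, and a hypothetical 10 of 11 detected has an exact 95% CI of 59% to 99.8%. Fifty participants may still serve for agreement on continuous analytes, which is a different question.

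**The case against.** The strongest reply is that the article never promises sensitivity or specificity. It speaks of validation by medical diagnosis, and confirming positives at a physician-attended examination is a real, if limited, form of validation. This stands. A reader might infer that part B validates nothing, and that would go too far: a confirmation rate is estimable and useful.

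Second, a reader might infer that the medical diagnosis is nothing more than Table 1 repeated on the same analyzer. The article does not say so. Part B adds a physician, a full history, a clinical examination and venous blood, and the full protocol may define the reference. What the article supports is narrower: the only MetS procedure it describes for part B is that of part A, and it names none of the additions as the MetS reference. A definition elsewhere would answer this part of the point, but would still leave the negatives unverified.

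Third, the pilot tests analyzers against a certified laboratory, so it would be wrong to say that the equivalence statement has no supporting comparison. For glucose and lipids it has one. For the electrocardiogram, cognitive and clinical examinations none is described. The pilot's success criterion is already confined to MetS components measured by point-of-care analyzers, and the equivalence sentence is an expectation in a Discussion, not an endpoint. These facts reduce the weight of this part of the point, but the pilot outcome sentence and the first aim remain wider than that criterion.

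Fourth, referral is conditional. That is so, but a MetS diagnosis is a stated reason for it, and everyone in part B has one.

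**Conclusion.** The outcome as worded claims more than the design can deliver. That sensitivity, specificity, negative predictive value and missed cases cannot be estimated from part B follows from its entry criteria alone. It rests on no assumed number, and no later analysis plan can recover these quantities from part B data.

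The sizes shown are illustrations. The range of 99% to 57% for sensitivity assumes 22% screen-positive, 90% confirmed and a true prevalence of 20% to 35%. The range of 0.56 to 1.00 for the observed confirmation rate assumes a predictive value of 0.80 and the extremes chosen for change and repeated error.

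The point should be fixed but is not fatal. Part A's prevalence outcome, the feasibility criteria, the cohort and part B's secondary-disease outcome do not depend on it, and no power calculation rests on it. What changes is the conclusion that may be drawn about the accuracy of the screening.

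**What to change.** 1. Restate the part B outcome as the confirmation rate on re-examination among part A positives without known secondary disease who are examined in the mobile unit. Report it with an exact 95% CI, together with the interval between parts A and B and any treatment newly started in between. State what counts as the medical diagnosis. Make no claim of sensitivity, specificity or validated screening from part B.
2. Limit the pilot's validity outcome, the matching first aim and the Discussion's equivalence statement to what the pilot compares with the reference laboratory: point-of-care glucose and lipids, and their effect on MetS classification, reported with a CI that reflects n = 50. Drop the claim for secondary-disease diagnostics.
3. Optional: if the stored part B serum is usable (the article does not give storage conditions in enough detail to tell), compare laboratory glucose and lipids with the point-of-care values from the same visit. This checks analyzer agreement at that visit only. It does not verify part A classifications or find missed cases.

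Items 1 and 2 cost wording and the recording of two extra items, with no new recruitment. Item 3 costs laboratory assays. The price is a more modest claim. Recruitment to part B was still open when the article was written, so the change can be made before its results are reported.
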